## Introduction

Chronic postsurgical pain (CPSP) is defined as chronic pain that persists over time (at least 3 months) following a surgical procedure and that has a significant impact on physical and psychosocial quality of life.^1 2^ Meta-analytical estimates in children and adolescents describe that around 25% of paediatric patients undergoing major surgery report chronic pain 3–12 months after surgery.^2^ Highest pain intensity ratings are observed in 2 weeks following surgery, with a steady decrease afterwards over the following 6 months,^3^ and pain ratings 2 weeks after surgery have been shown to predict the development of moderate to severe pain 1 year later.^4 5^ Further, most children and adolescents experience decreases in their physical activity levels following surgery, and it has been suggested that objectively monitored physical activity levels could be useful to indirectly assess functional recovery.^6^ A recent study in adolescents undergoing spinal fusion found that a majority of participants were characterised by a steep decrease of physical activity after surgery.^7^

Previous research has identified psychosocial risk factors that are associated with the development of CPSP, among them presurgical pain intensity, child anxiety, child pain coping efficacy, child sleep patterns and parental pain catastrophising.^2 8 9^ Generally, emotions and emotion-related factors are known to influence pain, pain-related disability and pain-related distress.^10 11^ There is some research on the role of emotion regulation in chronic pain,^12^ and the role of negative emotions is fairly well documented in the pain experience.^10 13 14^ However, other emotion-related factors such as emotion differentiation and emotion variability have yet to be studied in the context of paediatric CPSP, as they present as good targets for prevention and treatment modules and can be screened for in clinical practice.

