### Procedures

Potential participants will be informed about the study by the clinical collaborators at each study site during one of their presurgical visits (eg, anaesthesia preparation interview, scheduling visit). Based on the clinical routine of the study centres, the procedures might differ slightly. If patients fall within the required age range, the clinical collaborators will provide the family with a leaflet with the most important study information. On the leaflet, a QR-Code brings families directly to a site on the website of the University Children’s Hospital Zurich (main study centre), where they can find the most important information again. If families express their initial interest about the study, the physician will take a note and inform the study team, which will then contact the family. A member of the study team will then approach the respective family at their next visit at the hospital or via phone call and go through the informed consent/assent procedure with them. In all cases, parents sign the consent form for their own participation. In children under the age of 14 years, parents also sign the consent form for their child’s participation, while adolescents aged 14 years or more sign their own consent form. This is in line with the Human Research Act,^45^ which states that adolescents aged 14 years and more who are capable of judgement and who are to participate in a study with minimal risks can sign their own consent form. In participating hospitals, patients typically have (at least) two visits before the surgery. Once the written informed consent and assent is given, families will complete a battery of questionnaires as baseline measures before the surgery via direct link to the online questionnaires (see next section and table 1 for an overview; see online supplemental file 1 for an overview of reliability, validity, benefits and limitations of all questionnaires), using Research Electronic Data Capture (RedCap^46^). In addition, participants will be asked to download the smartphone application SEMA V.3,^47^ a free tool for ecological momentary assessment provided by the University of Melbourne, Australia, especially developed for research needs.

10.1136/bmjopen-2023-080174.supp1Supplementary data

**Table 1 T1:** Measures, tools, domain and time points for data collection

Domain		Measure	Completed by	BL	Post	FU 1	FU 2	FU 3

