Demographics	Age, gender, school, school attendance and performance; family constellation, parental educational level and work status	Parent and self-report: online baseline questionnaire	Parent(s) and child	X				
Medical history	Neonatal intensive care (yes/no), previous surgeries (yes/no; which one), child’s pain history (pain duration, pain location)	Parent report: online baseline questionnaire	Parents	X				
	Complications in the hospital (yes/no) Pain treatment immediately following surgery	Child’s medication list in electronic health record	Data entered by study team		X			
Experience-sampling method	Positive and negative emotions (emotion variability and emotion differentiation)*	Items from the Positive and Negative Affect Schedule^48^	Daily diary: child and parent	X	X			
	Pain severity	Numeric Rating Scale (NRS), 0–10	Daily diary: child	X	X	X		
Psychosocial factors child								
	Pain severity (intensity, distress, interference^77^)*	Numeric Rating Scale (NRS), 0–10	Child self-report				X	X
	Preoperative screening	Paediatric Pain Screening Tool^51 52^	Child self-report	X				
	Functional disability	Functional Disability Index^54^	Child self-report	X	X	X	X	X
	Fear of pain	Fear of Pain Questionnaire^53^	Child self-report	X				
	Pain catastrophising	Pain Catastrophising Scale—three-item version^78^	Child self-report	X				
	Attachment; parent–child relationship	Security Scale^79^	Child self-report	X				
	Symptoms of anxiety and depression*	Revised Child Anxiety and Depression Scale-short version^56^	Child self-report	X	X	X	X	X
	Sleep	Pittsburgh Sleep Quality Index^57^	Child self-report	X	X	X	X	X
	Sensory processing sensitivity	Highly Sensitive Child Scale^58^	Child self-report	X				
	Emotion regulation*	Emotion Regulation Questionnaire—Child and Adolescent version^19^	Child self-report	X				
	Quality of life	Paediatric Quality of Life Inventory^59^	Child self-report	X	X	X	X	X
	Social support	Social Support Questionnaire for Children^60^	Child self-report	X				
	Post-traumatic stress symptoms	Child and Adolescent Trauma Screening^80^	Child self-report	X		X		
Psychosocial factors parents								
	Parents’ own pain history	2 questions: ‘(1) Have you ever and (2) are you currently living with persistent or recurrent pain for at least 3 months?’	Parent self-report	X				
	Postoperative pain measure (child’s pain)	Postoperative Pain Measure for Parents^62^	Parent report		X			
	Fear of pain	Parent Fear of Pain Questionnaire^35^	Parent self-report	X				

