	Pain catastrophising	Pain Catastrophising Scale—three-item version^78^	Parent self-report	X				
	Anxiety and depression*	Anxiety and Depression Scale^63^	Parent self-report	X	X	X	X	X
	Sensory processing sensitivity	Highly Sensitive Person Scale^65^	Parent self-report	X				
	Emotion regulation*	Emotion Regulation Questionnaire^31^	Parent self-report	X				
	Quality of life	WHO Well-Being Index^66^	Parent self-report	X	X	X	X	X
Primary outcome								
Chronic postsurgical pain		Presence of CPSP: pain diary for seven consecutive days (NRS)+health-related quality of life (PedsQL, see above)				X		

*Primary predictors are marked with a *. Unmarked variables are considered secondary or exploratory.

BL, baseline; CPSP, chronic postsurgical pain; FU, follow-up; PedsQL, Paediatric Quality of Life Inventory.

Families will be called again 2 weeks after the surgery and asked to complete the postassessment via direct link to the questionnaires. Families will be contacted again 3 months (follow-up (FU) 1), 6 months (FU 2) and 12 months (FU 3) after surgery to complete the FU surveys and asked to complete the surveys at each assessment point within 1 week after receiving the link to the survey; up to 3-weekly reminders will be sent after the initial message.

In addition to the questionnaires at each assessment point, all participants (ie, children and parents) will complete daily diaries: To estimate the influence of emotion-related factors on pain trajectories, children and adolescents will complete two daily diary phases (ie, 2 weeks of daily diary) during which they rate both their pain severity and emotional state (referred to as ‘pain and emotions’ throughout the protocol; at baseline and postassessment), and one daily diary episode during which they only rate their pain intensity (referred to as ‘pain only’ throughout the protocol; at FU 1, see figure 1). Parents will complete two daily diary phases (at baseline and post) during which they exclusively rate their emotional state.

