### Statistical methods

Descriptive statistics will include mean and SD or median and IQR for normally distributed and non-normally distributed or ordinal variables measured at baseline. Categorical variables will be reported as number and percentage of total. The primary outcome is binary, therefore, generalised linear regression models or generalised linear mixed effects models will be used, using a logit link function. Fixed effects will be estimated for the primary predictors (as marked in table 1). Random effects will be included in the longitudinal model to account for repeated observations in the individual participants. The resulting estimands will be ORs and 95% CIs. Variables at baseline will be used in the prediction model, with performance measures area under the curve, calibration and scaled Brier Score.^71 72^ Variables measured consecutively over multiple days at each assessment interval will be averaged over time. We will use the rule of 10 EPV that would determine the number of independent variables in the regression model. Potentially time-varying covariates will be addressed. Potentially non-linear relationships of the independent variables with outcome will be evaluated. Further, the purpose of the multivariable regression analysis is to develop a risk score for CPSP. This will allow to identify variables that increase or decrease the risk for CPSP, by combining them into a multivariable model.

The preselected variables (ie, the primary predictors) will be assessed for collinearity with pair-wise scatter plots, pair-wise interaction terms will be included successively into the model. For the preselected variables, no variable selection will be performed. In an exploratory analysis, potential other variables will be evaluated and the process will be described in more detail in the statistical analysis plan.

Any missing values in the independent variables or the outcome will be addressed with 100-fold multiple imputation, using chained equations. Resulting estimates will be pooled using Rubin’s rule.^73 74^

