We will conduct bivariate analyses to compare study completers vs study dropouts to detect potential differences regarding participant demographic between the groups. Baseline daily pain ratings will be averaged for each participant to calculate a mean baseline pain intensity score. Postassessment and FU 1 daily pain ratings will be combined with health-related quality of life data to define binary outcome variables for acute postsurgical pain and CPSP. Acute postsurgical pain and CPSP will be defined independently.

For the trajectory analysis, the classification method K-means for longitudinal data will be used to determine clusters in the data (R package kml).^75^ The analysis of clusters joint trajectories (R package kml3d)^75^ will be applied, as this analysis allows summarising several correlated continuous variables into a single nominal variable.^76^ The trajectory analyses will be considered exploratory. Alternative clustering methods would be based on the risk score and participants with high risk for developing CPSP can be identified based on a cut-off of 10% predicted probability.

A detailed statistical analysis plan will be written up and finalised before data export for analysis. All analyses will be performed with the R programming language in a fully scripted way and dynamic reporting will be used to guarantee highest level of reproducibility.

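### The pain row starred as a primary predictor is collected only after the 3-month outcome, and baseline diary pain carries no star, so the primary model as written has no presurgical pain term

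*Protocol article*

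**What the plan says.** The assessment columns of Table 1 (Protocol article, Procedures) run "Completed by BL Post FU 1 FU 2 FU 3". Two rows concern the child's pain severity on the 0–10 scale:

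- The diary row, under the experience-sampling heading, reads "Daily diary: child X X X". It is collected at baseline, post and FU1, and has no star.
- The child self-report row, "Pain severity (intensity, distress, interference^77", has a star and is ticked at FU2 and FU3 only.

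The table footnote defines the star as marking primary predictors and adds: "Unmarked variables are considered secondary or exploratory". Study measures repeats the rule.

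Statistical methods ties the model to the stars: "Fixed effects will be estimated for the primary predictors (as marked in table 1". It also fixes their time point: "Variables at baseline will be used in the prediction model". It rules out variable selection among these preselected variables. Primary outcome places CPSP at FU1, which is 3 months after surgery. FU2 and FU3 are at 6 and 12 months.

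On baseline pain, Statistical methods says: "Baseline daily pain ratings will be averaged for each participant to calculate a mean baseline pain intensity score". It does not say where that score is used. The Introduction lists psychosocial risk factors for CPSP, "among them presurgical pain intensity, child anxiety, child pain coping efficacy" and others. The section on familial influences names preoperative pain intensity again, while noting that results were partly equivocal.

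**The concern.** The stars are the only definition of the primary model's content, so a star on the wrong row changes the model. The starred pain measure cannot serve as a baseline predictor of a 3-month outcome, because it is first taken at 6 months. The diary measure that could serve is classed as secondary or exploratory.

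Two uses of the model are affected. The first is to identify which emotion-related factors raise or lower the risk of CPSP. If presurgical pain is related both to CPSP and to an emotion index, and pain is not in the model, the index's odds ratio takes up part of the pain effect. The second is the risk score, which would lack a predictor that the authors themselves list among known risk factors.

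**Working it through.** **1. The two pain rows against the column headings**

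| Row | Star | BL | Post | FU1 | FU2 | FU3 |
|---|---|---|---|---|---|---|
| Pain severity, diary | no | X | X | X | – | – |
| Pain severity, child self-report | yes | – | – | – | X | X |

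The rows complement each other and agree with the diary schedule in Procedures, which has diaries at baseline, post and FU1 and none later. A fault in reading the table is therefore unlikely.

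**2. Timing.** First starred pain measurement: 6 months. Outcome: 3 months. The difference is 6 − 3 = 3 months after the outcome.

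**3. What the model contains if the text is followed.** Table 1 has six starred rows: diary emotions, pain severity, child anxiety and depression, child emotion regulation, parent anxiety and depression, and parent emotion regulation. Five have a baseline value. The sixth, pain severity, has none. The other baseline pain items, the Paediatric Pain Screening Tool and the child's pain history, are also unstarred. No presurgical pain term remains.

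**4. The predictor budget.** The plan's own figures reproduce: 280 × 0.25 = 70 events, and 70 / 10 = 7 predictors.

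- Counted by row: 5 usable starred rows plus baseline pain make 6, and 70 / 6 = 11.7 events per variable (EPV). This is within the limit.
- Counted by model term (an assumption, since the article does not fix the count): variability and differentiation for child and parent (4), anxiety/depression for child and parent (2), and two regulation strategies for child and parent (4) make 10 terms, and 70 / 10 = 7.0 EPV. Baseline pain makes 11, and 70 / 11 = 6.4 EPV. The limit of 7 is exceeded before pain is added.

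**5. Possible size of the bias.** The document gives neither the effect of presurgical pain on CPSP nor its correlation r with an emotion index, so both are assumed. For an index with no effect of its own, the approximate spurious OR per SD when pain is omitted is exp(r × ln OR of pain).

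| r | pain OR 1.8 | pain OR 2.0 |
|---|---|---|
| 0 | 1.00 | 1.00 |
| 0.3 | exp(0.3 × 0.588) = 1.19 | exp(0.3 × 0.693) = 1.23 |
| 0.5 | exp(0.5 × 0.588) = 1.34 | exp(0.5 × 0.693) = 1.41 |

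For scale, the OR per SD detectable with 80% power at two-sided 5%, for a single predictor and complete data, is about exp(√(7.849 / (280 × 0.25 × 0.75))) = exp(√(7.849 / 52.5)) = 1.47. This is not the power of the planned multivariable model.

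**The case against.** **The star is a labelling slip.** Procedures defines diary pain severity by the same three components as the starred row: intensity, distress and interference. The plan averages multi-day measures and builds a mean baseline pain score. The authors may well see one construct, split over two rows by mode of collection, with the diary supplying its baseline value. This is plausible, and it means that a deliberate omission of presurgical pain is not established. But no sentence assigns the baseline score to the primary model, and the star rule says the opposite. If it is a slip, it still has to be corrected, because the model is defined by the stars.

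**The star serves the longitudinal model.** The plan mentions mixed-effects models for repeated observations. However, CPSP as defined needs the 7-day diary, which is not scheduled at FU2 or FU3, so no later CPSP outcome exists for that pain to predict. Secondary outcomes lists pain severity as an endpoint.

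**The analysis plan will settle it.** A detailed plan is promised before data export and is a suitable place for the correction. But the article does not leave the primary set open. It fixes the set through Table 1, and what it fixes is contradictory.

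**Adjustment may be unwanted.** The Introduction says that emotions influence pain, so presurgical pain could be partly a mediator, and adjusting for it would remove part of the effect. This is a fair caution when interpreting the odds ratios. It carries no weight against including pain in a risk score.

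**The bias figures are assumed.** This stands. The section on emotion regulation cites studies that found no significant association with pain intensity, so r may be near 0. The other starred covariates would probably take up some of the association as well.

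**Stronger readings.** A reader might infer that a post-outcome variable will enter the model and inflate the AUC. The rule that baseline variables are used makes that unlikely. A reader might also infer that the diary is the only baseline source on pain. Table 1 ticks the screening tool and the pain history at baseline too, though both are unstarred.

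**Conclusion.** The contradiction between Table 1 and Statistical methods is real and rests on no assumption: one of six starred predictors has no baseline value and is first measured 3 months after the outcome. Applied literally, the primary model has no presurgical pain term, and every baseline pain item falls outside the primary set. This matters because the stars define both the primary model and the risk score.

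The effect on results is possible but cannot be quantified from the document. A spurious OR of 1.0 to about 1.4 per SD is the range for r from 0 to 0.5 with an assumed pain OR of 2.0. It shows what could happen and does not estimate a bias in this study. The sample-size arithmetic is not in error.

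**What to change.** Before the analysis plan is finalised:

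1. Move the star in Table 1 from the FU2/FU3 self-report row to diary pain at baseline.
2. State in Statistical methods that the mean baseline pain intensity score enters the primary CPSP model as one prespecified term.
3. State that pain at FU2 and FU3 is an outcome only and never a predictor of CPSP at FU1.
4. List the model terms that each starred row produces and count them against the 7 allowed at 10 EPV.

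No new data are needed, and the score is already planned. The cost is one degree of freedom from a budget that may already be full: 6 of 7 if counted by row, but 11 against 7 under the assumed expansion into terms. In the latter case the authors must reduce the prespecified terms or justify a different limit. The plan already announces that its EPV assumption will be re-evaluated.

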### Study measures

See table 1 for an overview, see online supplemental file 1 for an overview of reliability, validity, benefits and limitations of all questionnaires. For all measures, we use the validated German version (if available) or translate and back-translate the items with the help of a professional interpreter or native speaker. Measures of primary interest are marked with a * in table 1, all other variables are considered exploratory.

#### Child measures

Emotional state: The PANAS-C^48–50^ is a measure of positive and negative affect by providing mood adjectives (eg, ‘scared’, ‘happy’). Participants are asked to rate 10 items on a 5-point Likert scale from 1 (=very slightly or not at all) to 5 (=very much) to assess the extent to which they currently feel each of five positively and five negatively valenced emotions.

Pain screening tool: The Paediatric Pain Screening Tool^51 52^ entails nine self-reported items that belong to a physical and psychosocial subscale. Answers are given dichotomously (disagree=0, agree=1). Higher scores indicate higher risk status of poor pain-related outcomes.

Fear of pain: The Fear of Pain Questionnaire for Children (FOPQ-C)^53^ is a 24-item self-report inventory to assess fear of pain. Participants are asked to rate each item on a Likert scale from 0 (=strongly disagree) to 4 (=strongly agree). A higher total score indicates higher fear.

Functional disability: Children’s self-reported difficulty in physical and psychosocial functioning due to their physical health is assessed by the Functional Disability Inventory.^54^ 15 items are rated on a Likert scale from 0 (=no problems) to 4 (=not possible) and concern perceptions of activity limitations during the past 2 weeks. Higher scores indicate greater disability.

Security in parent–child relationships: The Security Scale^55^ consists of 15 items and assesses participants’ perceptions of security in parent–child relationships. Items are presented in a format of statements, participants choose which statement is more characteristic of them and then rate the statement on a Likert scale from 1 (=really true) to 4 (=sort of true). Higher scores indicate a more secure attachment.

Symptoms of anxiety and depression: The Revised Child Anxiety and Depression Scale-short version (RCADS-short version)^56^ is a 25-item self-report questionnaire used to assess symptoms of depression and anxiety. Participants are asked to indicate how often each item applies to them according to a 4-point Likert scale from 0 (=never) to 3 (=always). High scores indicate high anxiety and depression symptoms.

Sleep: The Pittsburgh Sleep Quality Index^57^ is the most commonly used retrospective self-report questionnaire that measures sleep quality over the previous month. We will use a version that has been slightly adapted for children by researchers of the University Children’s Hospital Zurich. This version contains of 25 items, and each item is rated on a scale from 0 (=no difficulty) to 3 (=severe difficulty). In addition to a global sleep quality factor, seven domains of sleep difficulties can be assessed: Sleep quality, sleep latency, sleep duration, habitual sleep efficiency, sleep disturbances, use of sleeping medications and daytime dysfunction. A higher global score indicates more sleep difficulties.

Sensory processing sensitivity: The Highly Sensitive Child Scale (HSC)^58^ is a 12-item self-reported questionnaire. Participants are asked to rate each item on a Likert scale from 1 (=not at all) to 7 (=extremely). In addition to a total score, three subscales can be calculated: low sensory threshold (LST; three items, eg, ‘I don’t like watching TV programmes that have a lot of violence in them’), Ease of Excitation (EOE; five items, eg, ‘I get nervous when I have to do a lot in little time’) and aesthetic sensitivity (AES; four items, eg, ‘I love nice smells’). Higher scores indicate higher sensitivity.

Emotion regulation: The Emotion Regulation Questionnaire for Children and Adolescents (ERQ)^19^ is a self-report questionnaire containing 10 items. Items are rated on a Likert scale from 1 (=strongly disagree) to 7 (=strongly agree), and assess individual differences in the habitual use of two emotion regulation strategies, namely cognitive reappraisal (eg, ‘When I’m faced with a stressful situation, I make myself think about it in a way that helps me stay calm’) and expressive suppression (eg, ‘I keep my emotions to myself’). Higher scores indicate more habitual use of the respective emotion regulation strategy.

Quality of life: The Paediatric Quality of Life Inventory (PedsQL)^59^ is a self-or parent-reported questionnaire for children and adolescents. 23 items are rated on a Likert scale from 0 (=never a problem) to 4 (=almost always a problem). The questionnaire consists of the subscales physical functioning (eg, ‘It is hard for me to run’), emotional functioning (eg, ‘I feel sad or blue’), social functioning (eg, ‘It is hard to keep up with my peers’) and school functioning (eg, ‘It is hard to pay attention in class’) in the past month. Higher scores indicate better quality of life.

Social support: The Social Support Questionnaire for Children^60^ consists of 50 items. It measures children’s social support across five distinct sources of support: parents, relatives, non-relative adults, siblings and peers. Items are rated on a 4-point Likert scale ranging from 0 (=never or rarely true) to 3 (=often or always true). Higher scores indicate higher levels of perceived support.

Symptoms of post-traumatic stress: The Child and Adolescent Trauma Screen 2^61^ contains a checklist of 15 potentially traumatic events (PTEs), followed by an item asking which of the PTEs bothers them most. Post-traumatic stress symptoms are measured by 20 items that are rated on a 4-point Likert scale ranging from 0 (=never) to 3 (=almost always). Five yes/no items assess whether the previously rated post-traumatic stress symptoms interfere with five key areas of functioning and are used to assess psychosocial functioning.

